#### 2.2.1. Sample Size Calculation

The required sample size will be estimated using the utility score of the Spanish version of the EQ-5D-3L questionnaire as primary outcome, and taken into account that this is an experimental study that will compare two groups with a significance level alpha = 0.05 and 80% of the statistical power that is required to detect a minimal clinically significant difference of 0.20 and SD = 0.12 [68].

On the other hand, we have also to consider the costs of the intervention added to the conventional care provided by the public health system, which will be 1680 € per caregiver. This amount will include the personal trainer’s salary, insurance, and 2 h/week travel-related costs.

A third aspect refers to the cost-efficiency ratio expressed as cost per quality-adjusted-life-years (QALYs). This will range between 10,000 and 50,000 € per QALYs [69], and we will use a conservative estimated sum = 30,000 € per QALYs. A cost-efficiency ratio = 0.21 corresponds to a 0.06 QALYs. In view of the above, a sample size of n = 50 caregivers distributed in two groups—control group and intervention group—is required to achieve a statistical power of 80% with a 95% of confidence interval, using an analysis of variance in parallel to parametric testing and anticipating a potential drop-out rate of 20%. In addition, in order to improve the confidence interval, a bootstrapping technique will also be used.

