### 2.5. Data Statistical Analysis

To determine possible inter-group differences in baseline data, the mean values of all baseline variables will be analyzed using independent sample t-tests. Moreover, for continuous variables with a normal distribution, we will use the Kolmogorov–Smirnov test and the correction of Lilliefors. For categorical variables, in turn, we will use the Pearson’s chi-squared test. In addition, inter-group differences will be analyzed using the Mann–Whitney U-test for continuous variables and the χ^2^ test for categorical variables. An analysis of variance will be also performed to determine inter-group differences regarding potential changes in the measured variables over the 9-months-long intervention period. Possible confounding factors, such as age, subjective burden, caregiver-rated Barthel Index, and length of caregiving-history at baseline, will be treated as dependent covariates. To determine the magnitude of change, effect sizes will be calculated using the pre-post-control (PPC) design [71]. The use of repeated measurements in the PPC design allows data from each individual to be used as his or her own control data, which typically increases the power and precision of statistical tests [72]. To determine the variable that best describes and predicts changes in different parameters, an adjusted multiple regression analysis will be performed. For all tests, the significance level will be set at *p* < 0.05. All statistical calculations will be performed using SPSS 18.0 (SPSS Inc., Chicago, USA).

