## 3. Outcomes

### 3.1. Primary Outcomes

#### 3.1.1. Health-Related Quality of Life and Cost-Utility

The main purpose of the analyses is to assess the cost-effectiveness of the targeted intervention, which is an intervention added to the conventional care. Therefore, the primary outcome will be the Spanish time trade-off utility of EQ-5D-3L (EQ-5D-3L utility) in terms of QALYs. The EQ-5D-3L [76] will be used to assess the general health status and the five dimensions of health-related quality of life: (1) mobility, (2) self-care, (3) daily activities, (4) pain and discomfort, and (5) anxiety and/or depression of participants. Each dimension is rated using a 1 to 3 level scale, where 1 = no problem, 2 = some problems and 3 = extreme problems. Using a combination of these different dimensions, it is possible to identify a total of 243 possible health states. At the end of the screening, we will obtain a total score of utility that will range from 1 = fully functional quality of life to 0 = death [77]. Participants’ data regarding the QALYs compiled 9 months and 12 months after the intervention will be used to make comparisons between the intervention group and the control group. In this way, we will be able to find potential differential changes in the QALYs of the participants as a function of whether they were subjected to the intervention or not. For this purpose, participants’ health utility curves will be calculated and compared among participants of both sample groups. We include a 12-months-long follow-up period, following the recommendations of the National Health Service (NHS). To avoid bias, data will be adjusted for differences in baseline EQ-5D scores via regression analysis [78].

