#### 3.1.4. Psychological Symptomatology

Psychological symptomatology will be measured using the Symptom Check List-90-R (SCL-90-R) [83]. This 90-item self-report questionnaire assesses the presence of psychological distress and a range of psychopathological symptoms. In particular, the SCL-90-R yields scores for nine primary symptom dimensions: somatization, obsessive-compulsive disorder, interpersonal sensitivity, depression, anxiety, hostility, phobic anxiety, paranoid ideation and psychoticism, as well as three indices of global distress. Each item is scored according to a 5-point Likert scale, which ranges from 0 = not at all to 4 = extremely. If the resulted global severity index is greater than or equal to a T score of 63th percentile or if the scores of two of those dimensions are greater than or equal to a T score of 63 or 75th percentile, this means that the respondent experiences severe symptomatology (positive case for caseness) [83].

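### The article names and sizes on one primary outcome, but lists five domains as primary and tests everything at 0.05

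*Protocol article*

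**What the plan says.** - **One primary outcome for sizing.** Section 2.2.1 derives the sample size "using the utility score of the Spanish version of the EQ-5D-3L questionnaire as primary outcome", for "two groups with a significance level alpha = 0.05 and 80% of the statistical power", and arrives at "a sample size of n = 50 caregivers distributed in two groups". No other outcome measure enters that calculation.
- **One primary outcome by definition.** Section 3.1.1 gives cost-effectiveness as the main aim and concludes that "the primary outcome will be the Spanish time trade-off utility of EQ-5D-3L (EQ-5D-3L utility) in terms of QALYs". It plans QALY comparisons at both 9 and 12 months, adjusted for baseline EQ-5D, and does not say which one decides.
- **Five domains by classification.** Section 3.1 (Primary Outcomes) also holds 3.1.2 burden (Zarit interview), 3.1.3 depression (GDS-15), 3.1.4 psychological symptoms (SCL-90-R) and 3.1.5 fitness. In 3.1.4, "the SCL-90-R yields scores for nine primary symptom dimensions", and there are three global indices besides. Section 3.2 (Secondary Outcomes) holds only adherence and adverse effects.
- **One threshold.** Section 2.5 plans an analysis of variance of between-group differences in change across the measured variables over the nine months. It then states: "For all tests, the significance level will be set at" p < 0.05. That section neither ranks the outcomes nor divides the alpha.

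**The concern.** A reader of the article cannot tell whether the trial has one primary outcome or five domains of them. This is not silence that an analysis plan could fill, because the article states both versions and fixes the threshold for all tests. If the section structure is followed, a significant burden score, symptom scale or balance test could be reported as a positive primary result even though the QALY comparison showed nothing. The authors want the results to inform health policy (sections 4 and 5), so it matters which result decides the trial and at what error rate. The sample size also gives no support to the other domains as primary outcomes, because no effect size or SD is stated for any of them.

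**Working it through.** **1. The plan's own figure.** Section 2.2.1 gives "minimal clinically significant difference of 0.20 and SD = 0.12". With two-sided alpha 0.05 and 80% power, n per arm = 2 × (1.960 + 0.842)² × (SD/difference)².

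- Difference 0.20: 2 × 7.85 × (0.12/0.20)² = 5.7, so 6 per arm, 12 in total, and 12/0.8 = 15 with 20% drop-out.
- Difference 0.06, the QALY figure in the same section, keeping SD 0.12: 2 × 7.85 × (0.12/0.06)² = 62.8, so 63 per arm, 126 in total, and 126/0.8 = 158 with drop-out.

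Neither gives 50. That is a separate matter and nothing below depends on it. What matters here is that only the EQ-5D-3L outcome was used for sizing.

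**2. The two classifications side by side.**

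| Domain | Sections 2.2.1 and 3.1.1 (text) | Section structure |
|---|---|---|
| EQ-5D-3L utility/QALY | the primary outcome | primary (3.1.1) |
| Burden | not named as primary | primary (3.1.2) |
| Depression | not named as primary | primary (3.1.3) |
| Psychological symptoms | not named as primary | primary (3.1.4) |
| Fitness | not named as primary | primary (3.1.5) |
| Adherence, adverse effects | – | secondary (3.2) |

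**3. How many tests.** With one test per domain there are 5. Counting the scores described gives QALY 1 + Zarit 1 + GDS-15 1 + SCL-90-R 12 (9 dimensions + 3 indices) + fitness 8 (BMI, waist/hip ratio, handgrip, flexor endurance, extensor endurance, sit-and-reach, flamingo, chair-stand) = 23. Using only the SCL-90-R global index reduces this to 1 + 1 + 1 + 1 + 8 = 12.

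**4. Chance of at least one false positive at 0.05 each, no true effects.** For independent tests this is 1 − 0.95^k:

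- k = 5: 1 − 0.774 = 22.6%
- k = 12: 1 − 0.540 = 46.0%
- k = 23: 1 − 0.307 = 69.3%

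The outcomes will be correlated, and the documents give no correlations. Simulated test statistics with a common correlation r (an assumption; 400,000 replicates for k = 5 and 200,000 for k = 23) give:

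| r | 5 tests | 23 tests |
|---|---|---|
| 0.3 | 21% | 58% |
| 0.5 | 18% | 45% |
| 0.7 | 15% | 31% |
| 0.9 | 10% | 16% |

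**5. With a sole primary outcome.** One test at one horizon has a false-positive rate of 5%, and the planned total stays at 50. If the 9- and 12-month QALY comparisons are both tested and either may count, the upper figure under independence is 1 − 0.95² = 9.75%. Positive correlation between the two horizons would bring it nearer to 5%.

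**The case against.** The article does rank its outcomes. Two separate statements, one of them with a reason, name the EQ-5D-3L outcome in the singular, and no sentence in 3.1.2 to 3.1.5 calls its measure a primary outcome. The label comes from position under a heading. In the SCL-90-R sentence the word primary describes the questionnaire's subscales, so it bears on the count and not on outcome status. The main cost-utility conclusion is reached by estimation (incremental ratio, bootstrap interval, acceptability curve), not by the 0.05 rule.

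Much of this stands, and it rules out three stronger readings that a reader might infer.

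- *That the 5% level fails for the trial's primary claim.* It fails only if the five domains are co-primary. Testing other scales does not change the error rate of the QALY comparison.
- *That the false-positive risk is 69%.* That is the upper figure under independence, and 12 of the 23 scores come from one questionnaire. The article does not say that each score gets its own confirmatory test.
- *That repeat testing at 9 and 12 months inflates the whole battery.* The article specifies those two comparisons for QALYs only. The analysis of variance covers change over the nine-month intervention.

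How multiplicity among secondary outcomes is handled is commonly left to an analysis plan, so its absence here is no fault.

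The objection does not remove the contradiction. A separate secondary section that leaves out burden, depression, symptoms and fitness classes them as primary as plainly as the singular sentences exclude them.

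**Conclusion.** The concern holds as an internal contradiction combined with an unqualified threshold. On the five-domain reading, the chance of a false-positive primary result is two to four and a half times the nominal 5% with one test per domain (10% to 23% for correlations from 0.9 down to 0). If all 23 scores are tested it runs from 16% to 69% over the same range. The five-domain range does not depend on how subscales are counted; both ranges rest on assumed correlations and on no true effect in any domain. On the single-outcome reading there is no inflation beyond the unresolved choice between 9 and 12 months. Because the text already favours that reading and the repair changes neither the primary analysis nor the planned sample size, this is a should-fix.

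**What to change.** 1. State that the baseline-adjusted EQ-5D-3L QALY, at one named horizon, is the sole primary outcome and is tested at 0.05. Present the other horizon as supportive.
2. Move 3.1.2 to 3.1.5 into section 3.2 as secondary outcomes.
3. Qualify the rule in section 2.5: p-values for the secondary outcomes are supportive unless a multiplicity procedure is prespecified. Holm on one score per domain (for example Zarit total, GDS-15 total and SCL-90-R global severity index, with one chosen fitness measure) is one option among several and can be left to the analysis plan.

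The cost is a relabelling and a sentence or two, ideally before outcome data are compared by group. The price is that results for burden, depression, symptoms and fitness can no longer be claimed as primary.

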#### Cost Utility Analysis

This analysis will be performed in two steps. First, the incremental mean costs of the exercise-based program, and the mean increase in QALYs secondary to the program, will be estimated using a health-care perspective. Second, the incremental cost-effectiveness ratio for the intervention will be calculated by dividing the incremental costs by the incremental QALYs.

To report uncertainty due to sampling variation, the 95% confidence interval will be calculated using the non-parametric bootstrapping technique (1000 replicates re-sampled with replacement from treatment and control populations), and a cost-effectiveness acceptability curve will be plotted [73,74]. This curve shows the probability that the intervention is cost-effective compared with the alternative across the range of values that decision makers are willing to pay to achieve an additional QALY. The “investment ceiling” is the maximum possible level of spending, even under the assumption of unlimited funding availability. For the health-care system in Spain, the current year adjusted investment ceiling was set at a conservative €30,000/QALY (30000 to 50000 E/QALY is normally accepted).

Decision makers should compare this upper limit of acceptable payment with estimated incremental cost-effectiveness ratios, to determine whether a given treatment is cost-effective relative to the alternatives.

A range of sensitivity analyses will be performed to explore the robustness of the estimates and to determine how dependent the results will be on estimates of participants’ unit costs and efficacy. The first analysis will examine the influence of participation rate in the program, as this could influence productivity by affecting the number of participants per unit of time provided by the personal trainer. A second analysis will explore the effects of cost fluctuations that might be take place due to changes in the salary of the physical trainer, since this is a major source of variability in economic studies [75]. The time and cost of travel from the research center to the participant’s residence will also be calculated. Finally, the robustness of cost utility will be assessed by analyzing different possible scenarios, combining the influence of variations in staff salary, rate of participation, distance to the participant’s home, and effectiveness, ranging from the lowest to the highest limit of the 95% confidence interval.

## 3. Outcomes

### 3.1. Primary Outcomes

#### 3.1.1. Health-Related Quality of Life and Cost-Utility

The main purpose of the analyses is to assess the cost-effectiveness of the targeted intervention, which is an intervention added to the conventional care. Therefore, the primary outcome will be the Spanish time trade-off utility of EQ-5D-3L (EQ-5D-3L utility) in terms of QALYs. The EQ-5D-3L [76] will be used to assess the general health status and the five dimensions of health-related quality of life: (1) mobility, (2) self-care, (3) daily activities, (4) pain and discomfort, and (5) anxiety and/or depression of participants. Each dimension is rated using a 1 to 3 level scale, where 1 = no problem, 2 = some problems and 3 = extreme problems. Using a combination of these different dimensions, it is possible to identify a total of 243 possible health states. At the end of the screening, we will obtain a total score of utility that will range from 1 = fully functional quality of life to 0 = death [77]. Participants’ data regarding the QALYs compiled 9 months and 12 months after the intervention will be used to make comparisons between the intervention group and the control group. In this way, we will be able to find potential differential changes in the QALYs of the participants as a function of whether they were subjected to the intervention or not. For this purpose, participants’ health utility curves will be calculated and compared among participants of both sample groups. We include a 12-months-long follow-up period, following the recommendations of the National Health Service (NHS). To avoid bias, data will be adjusted for differences in baseline EQ-5D scores via regression analysis [78].

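### The primary outcome compares QALYs at both 9 and 12 months without saying which decides, and near the plan's own cost-effectiveness ceiling the two horizons can give opposite verdicts.

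*Protocol article*

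**What the plan says.** The protocol article describes the EQ-5D outcome in several places.

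- **3.1.1 (primary outcome):** "the primary outcome will be the Spanish time trade-off utility of EQ-5D-3L (EQ-5D-3L utility) in terms of QALYs". The arms are then compared on both sets of data ("Participants’ data regarding the QALYs compiled 9 months and 12 months after the intervention will be used to make comparisons between the intervention group and" …, with controls as comparator). The 12-month follow-up is justified by an outside recommendation, and an adjustment for baseline EQ-5D is planned.
- **2.2.1 (sample size):** the trial is sized "using the utility score of the Spanish version of the EQ-5D-3L questionnaire as primary outcome", with a difference of 0.20 and SD 0.12 on the utility scale. A target of 0.06 QALYs is then added, with no horizon attached.
- **2.5 (analysis):** an analysis of variance is used "to determine inter-group differences regarding potential changes in the measured variables over the 9-months-long intervention period". "For all tests, the significance level will be set at *p* < 0.05".
- **Cost Utility Analysis:** "the incremental cost-effectiveness ratio for the intervention will be calculated by dividing the incremental costs by the incremental QALYs". No horizon is stated. The listed sensitivity analyses vary participation, salary, travel and effectiveness, but not the horizon.
- **2.4.2:** use of health services is recorded during the 9-month intervention.
- **Cost units (under 3.1.1):** effects are considered over a period of at most one year, which fits either horizon.

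**The concern.** Section 3.1.1 says that cost-effectiveness is the main purpose of the analyses, so the horizon of the QALY comparison bears on the main conclusion. The text points in two directions. The resource-use window and the analysis of variance point to 9 months; the reason given for the follow-up points to 12.

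The choice matters because the programme ends at month 9. Its cost is the same at both horizons, while any utility gain that persists continues to add QALYs until month 12. The two ratios therefore differ systematically, and not only through sampling error. If the horizon is chosen after the data are seen, the verdict against the ceiling may be chosen with it.

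**Working it through.** **Inputs from the protocol.** Programme cost EUR 1,680 per caregiver (2.2.1); ceiling EUR 30,000/QALY (Cost Utility Analysis); QALY target 0.06 and utility difference 0.20 (2.2.1); assessments at baseline, 3, 9 and 12 months (2.1).

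**Assumptions.** Visit months are counted from baseline; there is no between-arm difference at baseline; the utility gain d is constant at each later visit; QALYs are computed by the trapezoid rule; health-care costs are equal between arms.

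**The plan's own figure.** Break-even gain = 1680 / 30,000 = 0.056 QALY, which rounds to the stated 0.06.

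**QALY gain by horizon.**
- Months 0 to 3: 0.25 × (0 + d)/2 = 0.125d
- Months 3 to 9: 0.50 × d = 0.50d, so 0.625d by month 9
- Months 9 to 12: 0.25 × d = 0.25d, so 0.875d by month 12

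**Gain needed to meet the ceiling.** At 9 months, 0.056 / 0.625 = 0.0896. At 12 months, 0.056 / 0.875 = 0.064. Any constant gain between 0.064 and 0.0896 fails at 9 months and passes at 12.

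| Between-arm difference at 3, 9, 12 months | QALY to 9 | EUR/QALY at 9 | QALY to 12 | EUR/QALY at 12 |
|---|---|---|---|---|
| 0.08, 0.08, 0.08 | 0.0500 | 33,600 | 0.0700 | 24,000 |
| 0.08, 0.09, 0 (gain lost by month 12) | 0.0525 | 32,000 | 0.0638 | 26,353 |
| 0.10, 0.08, −0.12 (reversal after month 9) | 0.0575 | 29,217 | 0.0525 | 32,000 |
| 0.20, 0.20, 0.20 | 0.1250 | 13,440 | 0.1750 | 9,600 |

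**The 0.06 QALY target.** Read as accrued by month 12, it implies d = 0.06 / 0.875 = 0.0686. The ratio is 1680 / 0.06 = EUR 28,000 at 12 months (pass). At 9 months the gain is 0.625 × 0.0686 = 0.0429 QALY, about EUR 39,200 (fail). Read as accrued by month 9, d = 0.06 / 0.625 = 0.096; the ratios are EUR 28,000 at 9 months and 1680 / (0.875 × 0.096) = EUR 20,000 at 12 (both pass). The protocol does not say which reading applies.

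**Type I error.** Simulation under no effect, 20 completers per arm (50 less 20%, equal allocation assumed), 20,000 replicates. Between-visit correlation was assumed to be compound symmetric (0.3 to 0.8) or autoregressive (0.7 to 0.9 per 3 months). QALYs were adjusted for baseline.
- At least one of the two QALY tests significant at 0.05: 0.058 to 0.063
- At least one of three significant, adding the 9-month utility change: 0.081 to 0.100

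**The case against.** The strongest reply is that the article already leans to one reading. Section 3.1.1 states the primary outcome in QALYs, speaks of comparing utility curves and gives a reason for 12 months of follow-up, so the 9- and 12-month data could be points on one curve. A condensed article may also leave the base-case horizon to an analysis plan. Part of this stands: QALYs are the better-supported primary measure. But a utility curve still has to be integrated to some month, and the article does not leave the matter silent. It names two time points under one primary outcome and sets a 9-month cost window that fits only one of them.

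A reader might infer more than the documents support:

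- **That three contrasts compete as primary and nearly double the false-positive rate.** The analysis of variance in 2.5 is a general statement about all measured variables and never calls EQ-5D change primary. Without that contrast the rate is about 0.06.
- **That all three contrasts can give conflicting cost-effectiveness verdicts.** A 9-month utility change yields no cost per QALY. Only the two QALY horizons can conflict, and that verdict rests on the ratio, its bootstrap interval and the acceptability curve, not on p < 0.05.
- **That the plan's 0.06 is a utility gain inside the conflict band.** It is stated in QALYs. A utility gain of 0.06 would fail at both horizons: 1680 / 0.0375 = EUR 44,800 and 1680 / 0.0525 = EUR 32,000.

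**Conclusion.** The concern holds for the QALY horizon. As written, the main cost-effectiveness conclusion depends on an unchosen horizon, and a 12-month result would pair 12-month effects with 9-month health-service costs. With the plan's cost and ceiling, the verdicts conflict for constant utility gains of 0.064 to 0.0896. This is conditional: it rests on the assumed utility path and on no health-care offsets, and it disappears for effects well above the ceiling, such as 0.20. The usual direction is fail at 9 months and pass at 12; the reverse needs the effect to change sign after month 9. Inflated type I error is a lesser matter, about 0.06, reaching 0.08 to 0.10 only if the 9-month utility change is also treated as primary. The point should be corrected before data are seen.

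**What to change.** In 3.1.1, name one primary contrast and one horizon. An example is the between-arm difference in QALYs from baseline to month 12, adjusted for baseline EQ-5D utility, with the cost-utility result at that horizon as the base case. Label the other horizon a sensitivity analysis and the 9-month utility change supportive.

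Refer to the same contrast in 2.2.1 and 2.5. In 2.2.1 this means restating the power basis for the planned 50 participants on the chosen scale, since the SD of 0.12 is given for utility and none is given for QALYs; it does not require enrolling more.

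Collect costs over the same horizon. If month 12 is chosen, add resource-use questions covering months 9 to 12 at the 12-month visit already planned, and amend 2.4.2 to match.

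The cost is some rewording and, for month 12, a few extra questions at an existing visit. The downside is that a favourable result at the other horizon can no longer stand as the primary conclusion.
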